## Abstract

**Background:**

The Activity in GEriatric acute CARe (AGECAR) is a randomised control trial to assess the effectiveness of an intrahospital strength and walk program during short hospital stays for improving functional capacity of patients aged 75 years or older.

**Methods/Design:**

Patients aged 75 years or older admitted for a short hospital stay (≤14 days) will be randomly assigned to either a usual care (control) group or an intervention (training) group. Participants allocated in the usual care group will receive normal hospital care and participants allocated in the intervention group will perform multiple sessions per day of lower limb strength training (standing from a seated position) and walking (10 min bouts) while hospitalized. The primary outcome to be assessed pre and post of the hospital stay will be functional capacity, using the Short Physical Performance Battery (SPPB), and time to walk 10 meters. Besides length of hospitalization, the secondary outcomes that will also be assessed at hospital admission and discharge will be pulmonary ventilation (forced expiratory volume in one second, FEV_1_) and peripheral oxygen saturation. The secondary outcomes that will be assessed by telephone interview three months after discharge will be mortality, number of falls since discharge, and ability to cope with activities of daily living (ADLs, using the Katz ADL score and Barthel ADL index).

**Discussion:**

Results will help to better understand the potential of regular physical activity during a short hospital stay for improving functional capacity in old patients. The increase in life expectancy has resulted in a large segment of the population being over 75 years of age and an increase in hospitalization of this same age group. This calls attention to health care systems and public health policymakers to focus on promoting methods to improve the functional capacity of this population.

**Trial registration:**

ClinicalTrials.gov ID: NCT01374893.

## Background

Due to Western societies populations living longer there is a demand to explore new ways to promote healthy ageing instead of merely treating the diseases of old age [1]. According to the United Nations (average for the 2005–2010 period), Spain has the sixth longest life expectancy at birth in the world [2]. Therefore, especially in Spain, it is of public health and clinical relevance to better understand the effects of regular physical activity in old people. This is not only true for non-hospitalized individuals, but also includes hospitalized older individuals.

The negative effect of hospitalisation on functional outcomes in population-based [3] and in-hospital cohort studies is well-established [4,5]. This negative effect occurs even with short (several days) hospital stays [6-8]. Ten days of bed rest result in significant losses of whole body lean tissue, lower body lean tissue and strength in healthy 67-year-olds [7]. Loss of strength with bed rest can be as great as 5% per day [9]. With such significant losses of strength it is not surprising that even short hospital stays result in a decrease in functional capacity, including the ability to cope with activities of daily living (ADLs). In fact 30–50% of seniors admitted for a short hospital stay show a decrease in functional capacity at discharge [10-14]. These decreases in functional capacity are associated with an increased risk of mortality. For example, individuals showing the least decrease in functional capacity with a hospital stay have a mortality rate of 10.7% three months after discharge compared to 36.7% in individuals showing the greatest decrease in functional capacity [15].

As much as 73% and 83% of the measured hospital stay of older individuals is spent lying in bed [16,17]. During short hospital stays complete bed rest and low mobility levels are associated with negative functional outcomes [6,8]. Compared to patients with higher mobility levels, patients (mean age of ~79 years) who had complete bed rest or low mobility levels of all types (physical therapy, activity initiated by others, self initiated activity) during short hospital stays (5–8 days on average) showed greater declines in the ability to cope with ADLs, and greater risk of new institutionalization and death upon discharge and at 30 days after discharge [6,8]. The relationship between low mobility levels and negative functional outcomes is still significant after statistical multivariable adjustment for co-morbidity factors, such as severity of illness [6]. In contrast, the decline in negative outcomes with higher mobility levels follows a dose–response effect [8].

A recent meta-analysis concluded that intrahospital programs with the goal of maintaining or increasing functional capacity in hospitalized seniors result in decreased mortality rates, decreased length of hospitalization and decreased rates of discharge to nursing homes compared to discharge to home [18]. This indicates mobility and physical training are modifiable factors that have important implications for care regimes. Loss of lower body muscle mass is a strong predictor of physical performance and functional capacity in seniors [19], indicating physical training programs should emphasize the lower body musculature. Therefore, it is important to determine if increased mobility and physical training, especially of the lower body, have an effect upon functional outcomes during short hospital stays in older individuals.

### Objectives

The purpose of the proposed research [acronym: AGECAR (Activity in GEriatric Acute CARe)] is to investigate the effect of an intrahospital multi-time per day physical training program, consisting of walking and strength training of the lower limbs, during a short period of hospitalization in seniors aged 75 years or older on functional capacity at discharge (primary outcome). The effect of the physical training program will be compared to a control group receiving normal hospital care. Besides length of hospitalization, the secondary outcomes that will also be assessed at hospital admission and discharge will be pulmonary ventilation (forced expiratory volume in one second, FEV_1_) and peripheral oxygen saturation. The secondary outcomes that will be assessed by telephone interview three months after discharge will be mortality, number of falls after discharge, and ability to cope with activities of daily living (ADLs, using the Katz ADL score and Barthel ADL index).

Increased age and a history of falls in the previous year are associated with decreased functional capacity [11], and handgrip strength is a predictor of survival [20] and mobility [21]. On the other hand, low cognitive ability, reflected as low scores on the Mini-Mental Status Examination (MMSE) is associated with increased chance of decreased functional capacity upon discharge [11,22]. Thus, we will also determine if age, history of falls in the previous year, handgrip strength and MMSE scores (covariates) will have an influence on the effects of the training program on the aforementioned primary and secondary outcomes. The major hypothesis is the prescribed training program will increase functional capacity at discharge while decreasing length of hospitalization.

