### Covariates

Besides actual blinding success of assessment staff to participant randomisation assignment, the following covariates will be measured in all participants upon hospital admission as they could influence one or more of the study outcomes.

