### Statistical analysis

To assess the training effects on the study outcomes, we will analyze the data according to the intention-to-treat principle [37]. When post-test data are missing, baseline scores will be considered post-test scores. We will use a two-factor (group and time) analysis of variance (ANOVA) with repeated measures. We will repeat the analysis using the actual blinding of assessment staff to participant randomisation assignment (successful or not), baseline values of age, body mass index, MMSE, number of falls within the previous year and handgrip strength as covariates. For each outcome variable we will report the level of significance corresponding to the main group (between-subjects), time (within-subjects) and interaction (group × time) effects. We will perform post hoc pre- vs. post comparisons by group only when a significant group*time effect is present. The level of significance will be set to = 0.05. We will adjust multiple comparisons for mass significance [38]. We will use the Student’s *t* test (or its non-parametric equivalent, the Mann Whitney’s *U* test) for comparing between the two groups the mean values of those secondary outcomes that will be assessed only once, i.e. three months after discharge (number of falls, Katz score and Barthel index). We will compare mortality rate at three months after discharge in the two groups with the chi square test.

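### The aim of finding whether age, falls history, handgrip and MMSE alter the training effect has no analysis that can answer it: they enter only as adjustment covariates

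*Protocol article*

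**What the plan says.** The Objectives section of the protocol article sets a further aim, to "determine if age, history of falls in the previous year, handgrip strength and MMSE scores (covariates) will have an influence on the effects". The effects in question are those of training, and the sentence extends them to every primary and secondary outcome. The aim therefore names four baseline variables and covers all outcomes.

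The Covariates section gives a different reason for measuring such variables: "as they could influence one or more of the study outcomes".

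The Statistical analysis section states the model: "We will use a two-factor (group and time) analysis of variance (ANOVA) with repeated measures". That analysis is then repeated with assessor-blinding success and "baseline values of age, body mass index, MMSE, number of falls within the previous year and handgrip strength as covariates". For each outcome the results to be reported are the "main group (between-subjects), time (within-subjects) and interaction (group × time) effects".

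A t test or Mann-Whitney U test is planned for "those secondary outcomes that will be assessed only once, i.e. three months after discharge (number of falls, Katz score and Barthel index". For deaths the text is: "We will compare mortality rate at three months after discharge in the two groups with the chi square test". None of these three-month comparisons includes a covariate.

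**The concern.** In the aim, the thing influenced is the effect of the programme, not the outcome. That asks whether training works better or worse in older patients, in those with weaker grip or lower cognition, or in those who have fallen. A covariate entered for adjustment answers other questions: whether it predicts the outcome or its change, and what the average training effect is once it is held fixed. The adjusted model assumes the same training effect at every covariate value.

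What is at stake is one declared, ancillary aim. Followed as written, the trial would finish with no estimate for it. The nearest available output would be a shift in the group × time result between the unadjusted and adjusted runs, and that shift does not measure effect modification.

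**Working it through.** **1. Match the aim to the planned terms.** In a group × time model on admission and discharge scores, the training effect is the group × time term. For that effect to depend on a covariate, the model needs group × time × covariate, or group × covariate when the change score is analysed.

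| Term | What it estimates | In the stated plan? |
|---|---|---|
| Group × time | average training effect | yes, reported |
| Covariate | prognosis | entered, not listed for reporting |
| Covariate × time (added by some software) | prediction of change, pooled over arms | not stated |
| Group × time × covariate | change in training effect with the covariate | no |

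For three-month falls, Katz, Barthel and mortality, the tests are two-group comparisons with no covariate.

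**2. Check that the covariate-only model does not reveal moderation.** The simulation used 3,000 runs per scenario, 60 patients per arm, a standardised change score, a main effect of 0.511 SD and a covariate with no average prognostic effect.

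| True moderation (SD per SD of covariate) | Adjusted group effect | Covariate term significant | Group × covariate term significant |
|---|---|---|---|
| 0 | 0.52 | 5.1% | 4.5% |
| 0.5 | 0.51 | 5.6% | 74.5% |

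The outputs of the covariate-only model are almost the same whether or not moderation exists. Only the interaction term separates the two cases.

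**3. Inputs for precision.** The Sample size and statistical power section gives two groups of 60, significance level 0.05, power above 80%, and 20% loss. Its recruitment figure reproduces: 120 / (1 − 0.20) = 150. It gives no SD and no baseline SPPB, so the 60 per group cannot be reproduced. Assuming a two-sided test and exactly 80% power, 60 per group corresponds to a standardised difference of

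(1.960 + 0.842) × √(2/60) = 2.802 × 0.1826 = 0.511 SD.

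**4. Continuous moderator, n = 120.** The SE of the interaction per SD of the covariate is √(4/120) = 0.183. The smallest interaction detectable with 80% power is 2.802 × 0.183 = 0.51 SD per SD. This depends on n only, not on the assumed main effect.

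**5. Binary moderator with share q, n = 120.** SE = √(4 / (120 × q × (1 − q))). Power for an interaction equal to the main effect is Φ(0.511/SE − 1.960).

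| Split | SE | Power | Detectable at 80% power |
|---|---|---|---|
| 50/50 | 0.365 | 29% | 1.02 SD |
| 30/70 | 0.398 | 25% | 1.12 SD |
| 20/80 | 0.456 | 20% | 1.28 SD |

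**6. Multiplicity.** Four unadjusted moderator tests on one outcome, if independent, give a chance of at least one false positive of 1 − 0.95⁴ = 18.5%.

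Steps 3 to 5 treat patients as independent. Allocation by four-week block lowers the effective sample size, so the true figures are likely to be worse.

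**The case against.** The strongest reply is that the Objectives sentence is loosely worded and only adjustment was meant. The lines leading up to it are prognostic: age and falls go with lower function, grip predicts survival and mobility, and low MMSE goes with functional loss at discharge. The sentence itself labels the variables as covariates, and the Covariates section gives a prognostic reason for collecting them. Read this way, the sections form one adjustment plan. This reading is possible and cannot be excluded, but the literal object of the sentence is the effect of the programme. If adjustment was meant, the sentence still needs correcting.

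A second reply is that moderator detail belongs in an analysis plan that is not shown. That carries little weight here, because the article itself says how these variables will be used and which effects will be reported, and this does not match the aim.

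A reader might also infer that the trial will report a significant MMSE or handgrip coefficient as showing who benefits from training. The document does not support that. Covariate coefficients are not among the effects listed for reporting, and nowhere does the text say they will be interpreted as moderation.

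**Conclusion.** The point holds as a mismatch between a stated aim and a stated analysis. Taken literally, the aim concerns effect modification on all primary and secondary outcomes. No planned term estimates it for the admission-to-discharge outcomes, and the three-month outcomes have no covariate analysis at all. This conclusion is structural and does not depend on the power figures.

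The consequence is limited. The aim is ancillary, and the group × time comparison of the primary outcomes is untouched. It would be wrong to infer that the main result is biased or invalid.

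The power figures show only how precise a corrected analysis could be. They rest on 120 independent evaluable patients and a two-sided 0.05 test. The 20–29% range also assumes a main effect of about 0.51 SD and applies to a binary factor. For covariates kept on their continuous scale, the relevant figure is about 0.51 SD per SD detectable with 80% power.

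**What to change.** In the Statistical analysis section, add a group × time × covariate term with its lower-order terms, for SPPB and the 10-metre walk. The same question can be put as group × covariate on the change score or on the baseline-adjusted discharge score. Fit one covariate at a time, on its continuous or count scale: age, number of falls in the previous year, handgrip strength and MMSE. Report each interaction estimate with its 95% confidence interval, label it exploratory, and state that four such tests are made per outcome. Keep the existing covariate-adjusted run as a separate adjustment analysis.

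In the Objectives section, limit the aim to those two outcomes. If only adjustment was intended, leave the analysis as it is and reword the aim to say that the training effect will also be estimated after adjustment for these variables.

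The first option needs four interaction models per primary outcome, fitted to data already being collected. Its drawback is wide intervals, so an interval that includes zero should not be read as evidence of a uniform effect. The second option costs one sentence.

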### Secondary outcome measures

#### *Length of hospitalization*

We will assess length of hospitalization (in days).

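### The admission covariates enter only the repeated-measures ANOVA, so three-month Katz, Barthel and falls are compared unadjusted, and length of stay fits neither analysis route

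*Protocol article*

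**What the plan says.** The Objectives section gives reasons why age, previous falls, handgrip strength and MMSE matter for function or survival. It says the trial will determine whether they "will have an influence on the effects of the training program on the aforementioned primary and secondary outcomes". The Covariates section states that "the following covariates will be measured in all participants upon hospital admission as they could influence one or more of the study outcomes", and the SPPB is also taken at admission (Primary outcome measures).

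The Statistical analysis section sets out the methods in this order:

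- Main model: "We will use a two-factor (group and time) analysis of variance (ANOVA) with repeated measures".
- Covariates, a little further on: "We will repeat the analysis using the actual blinding of assessment staff to participant randomisation assignment (successful or not), baseline values of age, body mass" (that is, BMI; the list goes on to cognition, previous-year falls and grip strength). Admission SPPB is not on this list.
- Outcomes measured once: a t or Mann-Whitney test, whose stated purpose is "comparing between the two groups the mean values of those secondary outcomes that will be assessed only once". The outcomes meant are the ones "assessed only once, i.e. three months after discharge (number of falls, Katz score and Barthel index").
- Three-month mortality: chi-square test.

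Length of hospitalization is a secondary outcome recorded in days, and its reduction is part of the major hypothesis in Objectives. Statistical analysis does not mention it.

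**The concern.** A group-by-time ANOVA needs an admission and a discharge value. Katz, Barthel and falls at three months have one post-discharge value each, so the covariate-adjusted repeat of that ANOVA cannot be applied to them, and the tests they do receive take no covariates. Values that the protocol itself calls prognostic are collected on every patient and then not used for these outcomes.

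Two things are at stake. The residual variance is larger than it need be, so a real effect on daily living is easier to miss. Chance differences between arms in age, cognition or admission function also stay in the comparison. The second matters more than usual here, because whole four-week admission periods share an arm and few such periods exist.

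Length of stay has one value per patient, so the ANOVA cannot take it, and it is not among the three-month outcomes given the t or Mann-Whitney test.

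**Working it through.** **Which outcome has a route to adjustment**

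| Outcome | Values per patient | Method in Statistical analysis | Covariates possible as written |
|---|---|---|---|
| SPPB, 10 m walk, FEV1, oxygen saturation | admission and discharge | group × time ANOVA, repeated with covariates | yes |
| Katz, Barthel, falls | one, at three months | t or Mann-Whitney | no |
| Mortality | one, at three months | chi-square | no |
| Length of stay | one, at discharge | none that fits | no |

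**The plan's own figure.** Sample size and statistical power gives two groups of 60 and 20% loss: 120 / (1 − 0.20) = 150, which reproduces. The 60 per group cannot be reproduced, because no SD is given. At 60 per arm, two-sided alpha 0.05 (sidedness assumed) and 80% power, the detectable standardised difference is (1.960 + 0.842) × √(2/60) = 0.511. This is the reference point below. The trial was sized on SPPB, not on the ADL scores.

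**Gain from adjustment.** With covariates explaining a share R² of the outcome variance, the residual SD is multiplied by √(1 − R²). Then power = Φ(0.511 / [√(1 − R²) × √(2/60)] − 1.960), and the equivalent sample size is 60 / (1 − R²) per arm. R² is assumed, since the document gives none. The last column is a simulation (4,000 runs, five covariates, independent patients), which also counts the lost degrees of freedom.

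| R² (assumed) | Equivalent n per arm | Power by formula | Simulated: t test → adjusted |
|---|---|---|---|
| 0 | 60 | 80.0% | 78.7% → 76.5% |
| 0.1 | 66.7 | 84.0% | 79.1% → 82.0% |
| 0.2 | 75 | 87.9% | 79.4% → 85.7% |
| 0.3 | 85.7 | 91.8% | 80.4% → 91.2% |
| 0.4 | 100 | 95.1% | 80.3% → 94.0% |

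By formula the gain is about 4, 8, 12 and 15 points at R² 0.1, 0.2, 0.3 and 0.4. By simulation it is about 3, 6, 11 and 14 points, with a loss of about 2 at R² 0.

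**Imbalance.** Under patient-level allocation, a standardised covariate has a between-arm standard error of √(2/60) = 0.183. If its correlation with the outcome is 0.4 to 0.6 (assumed), an imbalance of one standard error moves the raw difference by 0.183 × 0.4 = 0.07 to 0.183 × 0.6 = 0.11 SD.

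**Blocks.** Four weeks plus a one-week gap is five weeks per block. June 2012 to June 2013 is about 52 to 56 weeks, so 52/5 = 10.4 to 56/5 = 11.2, or roughly 10 to 11 blocks in all. The table and the imbalance figure treat patients as independent and so do not describe this design in absolute terms.

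**The case against.** An unadjusted comparison of a randomised secondary outcome is a legitimate analysis, and the Covariates section says only that these variables could influence one or more outcomes. It does not commit the trial to adjusting all of them. The article is condensed, and adjusted secondary models may be set out in a fuller plan. The R² range is an assumption. At R² 0 adjustment costs a little, and at 0.1 it gains only 3 to 4 points. Much of this stands. It limits the point to an avoidable inefficiency and means that no single gain can be claimed. It does not remove the point, because the article does fix the tests for Katz, Barthel and falls, and fixes them without covariates.

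The instruction to repeat the analysis could be read as covering every outcome. Its position, after the ANOVA and before the once-only tests, and the fact that those tests take no covariates make that reading unlikely.

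Three stronger readings are tempting, and the document does not support them:

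- A reader might take the Objectives sentence as a promise to adjust every outcome for precision. It concerns whether covariates modify the training effect, which is a different question.
- A reader might say that length of stay is compared without covariates. No comparison is named for it, so no precision loss can be attached to one.
- A reader might quote the power figures as this trial's power. They assume independent patients and a chosen R².

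**Conclusion.** The point holds in a limited form. As written, three-month Katz, Barthel and falls are compared without baseline values that are already collected, and length of stay has no place in either analysis route although it is in the major hypothesis. Mortality also carries no covariates. The variance calculation above does not apply directly to a binary outcome, so the point is not extended to it.

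The direction of the gain is clear for any non-trivial R², but its size cannot be obtained from the document. The range runs from a loss of about 2 points of power at R² 0 to a gain of about 15 at R² 0.4. That range assumes a continuous outcome, 60 independent patients per arm and 80% unadjusted power. For bounded ADL scores and fall counts it is indicative only. Patient-level covariates remove between-block variation only in part, so adjustment lessens the risk of imbalance from block allocation and does not cure it.

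Main-effect adjustment does not answer the effect-modification question in Objectives. That would need arm-by-covariate terms, and Statistical analysis names none for any outcome. These are secondary outcomes and the change costs almost nothing, so it should be made, but the validity of the trial does not depend on it.

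**What to change.** In Statistical analysis, name the reported comparison for each of these outcomes:

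- Katz and Barthel: a linear or proportional-odds model.
- Number of falls: a count model.
- Length of stay: a model on log days or on time to discharge.

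Each model should include arm plus admission SPPB, age, MMSE, handgrip strength and previous-year falls. Keep the t or Mann-Whitney tests as supportive. Leave blinding success out of this baseline set: it arises after allocation and belongs in a separate sensitivity analysis. If the effect-modification objective is kept, state the arm-by-covariate terms that will address it and label them as a separate analysis.

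The cost is wording only, with no new data, patients or visits. A few patients may lack a covariate and need a simple, pre-stated imputation.
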